**Hypotheses**

Project hypotheses focus on the effectiveness of the prevention intervention package on behavioral outcomes, biologic outcomes, and delivery of services in the HIV care and treatment settings. Intervention clinics will integrate the HIV prevention intervention package into routine care of HIV-positive patients; comparison clinics will provide standard of care to HIV-positive patients.

Compared to participants attending comparison HIV clinics, participants at intervention clinics will be more likely over a 12-month period to report or show a(n):

Behavioral

- Decrease in unprotected vaginal and anal sex
- Decrease in number of sex partners
- Increase in number of sex partner(s) getting an HIV test
- Increase in disclosure of HIV status to sex partner(s)
- Decrease in alcohol use
- Increase in adherence to HIV antiretroviral medications

Biologic

- Decrease in unintended pregnancy or partner pregnancy
- Decrease in STIs (i.e., urethral discharge)

Service Delivery

Compared to the comparison clinics, the intervention clinics will:

- Provide more family planning counseling (e.g., safer pregnancy) and services (e.g., contraception) to HIV-positive women and their partners

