- Counseling discordant couples on risk reduction strategies such as negotiating condom use, correct and consistent condom use, and supporting each other with health-related issues (e.g., adherence, alcohol use).

Using the 5As model adapted from the WHO IMAI training (WHO, 2004), prevention counselors will be trained to “assess, advise, agree, assist, and arrange” during the counseling sessions. For example, the lay counselor will *assess* the nature of the high risk behavior and offer information and make recommendations to the patient (*advise*). The lay counselor and patient will *agree* together on a behavior to change. The lay counselor will *assist* the patient in developing behavior change steps and resolving potential barriers to successfully changing the identified behavior. Finally, the lay counselor will *arrange* or organize any components necessary to help the patient meet the goal, as well as arrange another visit to continue addressing these issues.

In addition, where the local government allows, lay counselors will administer rapid HIV tests to sex partners of HIV-positive patients. The lay counselor will give each patient a slip to give to their partner if their partner has not been tested or needs to be re-tested. This slip encourages the partner to get tested for HIV and indicates where this can be done. Patients will be told that the contact slips should be brought back to the clinic when the partner comes in for testing in order to track partner testing. The counselor will refer any partner who tests HIV-positive immediately to the HIV clinic for care and treatment.

Lay counselors will also be trained to conduct group education sessions in the clinics and support groups (where appropriate). These educational sessions will deliver key prevention and healthy living messages to HIV patients who may not be seen by counselors for individual counseling sessions. Topics covered in these educational and/or group sessions will include:

- Basics of HIV
- Treatment of HIV and Adherence
- Prevention of Sexual Transmission of HIV
- Prevention of transmission to unborn children (PMTCT, family planning)
- Healthy Living (prevention of opportunistic infections, safe water and food, personal hygiene, coping and emotional support)
- Nutrition and exercise

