Project enrollment will occur over of a 2-3 month period at both intervention and comparison clinics. Following completion of the baseline data collection, the intervention will be implemented at the intervention clinics. Because of the baseline data collection period, the 6-month follow-up will be scheduled for a time estimated to be 6-months after the intervention is integrated into the clinic, so that all intervention clinic participants will have an opportunity to be exposed to the intervention following staff training and implementation. To make the intervention and comparison clinic project procedures as similar as possible, the intervention and comparison clinic 6-month follow-up interviews will occur during the same time period. The same battery of questionnaires will be administered to participants at the 6- and 12-month follow-up interviews, with the exception of some of the sociodemographic questions and items asking about whether something had “ever” happened. At each follow up interview, participants will be offered a soda or other drink and reimbursed for travel costs to the clinic upon completion of the interviews.

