**Appendix H**

**Patient Questionnaire**

HIV Prevention for People Living with HIV/AIDS

Baseline Questionnaire

***Interviewer reads:* “**Thank you for agreeing to meet with me today and participate in this project. Taking part in the survey is up to you. All of the responses that you give will be kept private and will not be shown to others. I will ask you questions that may be uncomfortable to answer. You are free to not answer any questions that you feel are too personal. However, if you take part, you will help us understand more about how to help keep people with HIV healthy and prevent the spread of HIV. If I ask questions you don’t want to answer, just let me know and I will go on to the next question. You can stop the interview at any time. Our meeting will last about 1 hour. Do you have any questions?”

Patient ID #: ______________________

Interviewer ID #: ______________________

Interview Start Time: _________________

Interview End Time: _________________

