**Patient Sex Behavior**

| ***Interviewer reads:*  “**Now I would like to ask you some questions about your recent sexual activity. We know these questions are sensitive and want to remind you that your answers are completely private and will not be shared with anyone. No one will know what particular answers you give. It is perfectly normal for persons with HIV to have sex. We are not judging you on your sexual behaviors. We want you to be as honest as you can answering these questions. If we should come to any questions that you don’t want to answer, just let me know and we will go to the next one.  Different people have different definitions of ‘sex’ or ‘sexual intercourse.’ For this study, sex can include several things, such as:   - Vaginal sex, which is when a man puts his penis in a woman’s vagina. - Anal sex, which is when a man puts his penis in another person’s rectum or butt.” |
| --- |

J1. How old were you when you had sexual intercourse for the very first time?

__________Age in years

*_____-1. Don’t know*

*_____-2. Refused*

J2. In total, how many different people have you had sexual intercourse with in your entire life?

__________Total number of lifetime partners

*_____-1. Don’t know*

*_____-2. Refused*

J3. Have you had sexual intercourse in the last 3 months?

_____ 0. No  *Skip to K1 in next section.*

_____ 1. Yes

*_____-1. Don’t know*

*_____-2. Refused*

J4. In total, how many people have you had sex with in the last 3 months?

__________ Total number of partners

*_____-1. Don’t know*

*_____-2. Refused*

J5. In total, how many people have you had sex with in the last 2 weeks?

__________ Total number of partners

*_____-1. Don’t know*

*_____-2. Refused*

| ***Interviewer reads:*** “I am going to ask you about the people you had sex with over the past 90 days. Please tell me about them starting with your most recent sexual partner.” |
| --- |

*[****Interviewer:*** *Read down each column of the table (for each partner, one at a time),* ***not*** *across each row.]*

|  | **Partner 1** | **Partner 2** | **Partner 3** | **Partner 4** | **Partner 5** |
| --- | --- | --- | --- | --- | --- |
| J6. What is the first name or a nickname of this partner? | ___ *-1. Don’t know*  ___ *-2. Refused* | ___ *-1. Don’t know*  ___ *-2. Refused* | ___ *-1. Don’t know*  ___ *-2. Refused* | ___ *-1. Don’t know*  ___ *-2. Refused* | ___ *-1. Don’t know*  ___ *-2. Refused* |

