| J10. Are you still in a sexual relationship with this partner? | ___ 0. No  ___ 1. Yes  ___ *-1. Don’t know*  ___ *-2. Refused* | ___ 0. No  ___ 1. Yes  ___ *-1. Don’t know*  ___ *-2. Refused* | ___ 0. No  ___ 1. Yes  ___ *-1. Don’t know*  ___ *-2. Refused* | ___ 0. No  ___ 1. Yes  ___ *-1. Don’t know*  ___ *-2. Refused* | ___ 0. No  ___ 1. Yes  ___ *-1. Don’t know*  ___ *-2. Refused* |
| J11. Since you first had sex with this partner, how many other people have you had sex with during the sexual relationship? | _______ [# of partners]  ___ *-1. Don’t know*  ___ *-2. Refused* | _______ [# of partners]  ___ *-1. Don’t know*  ___ *-2. Refused* | _______ [# of partners]  ___ *-1. Don’t know*  ___ *-2. Refused* | _______ [# of partners]  ___ *-1. Don’t know*  ___ *-2. Refused* | _______ [# of partners]  ___ *-1. Don’t know*  ___ *-2. Refused* |
| J12. Has this partner been tested for HIV? | ___ 0. No** J16**  ___ 1. Yes  __*-1.Don’t know***J16**  __ *-2. Refused*** J16** | ___ 0. No** J16**  ___ 1. Yes  __*-1.Don’t know***J16**  __ *-2. Refused*** J16** | ___ 0. No** J16**  ___ 1. Yes  __*-1.Don’t know***J16**  __ *-2. Refused*** J16** | ___ 0. No** J16**  ___ 1. Yes  __*-1.Don’t know***J16**  __ *-2. Refused*** J16** | ___ 0. No** J16**  ___ 1. Yes  __*-1.Don’t know***J16**  __ *-2. Refused*** J16** |
| J13. How long ago was this partner tested for HIV? | ____ Days ago  ____ Months ago  ____ Years ago  ___ *-1. Don’t know*  ___ *-2. Refused* | ____ Days ago  ____ Months ago  ____ Years ago  ___ *-1. Don’t know*  ___ *-2. Refused* | ____ Days ago  ____ Months ago  ____ Years ago  ___ *-1. Don’t know*  ___ *-2. Refused* | ____ Days ago  ____ Months ago  ____ Years ago  ___ *-1. Don’t know*  ___ *-2. Refused* | ____ Days ago  ____ Months ago  ____ Years ago  ___ *-1. Don’t know*  ___ *-2. Refused* |
| J14. Do you know this partner’s HIV status? | ___ 0. No** J16**  ___ 1. Yes  __*-1.Don’t know***J16**  __ *-2. Refused*** J16** | ___ 0. No** J16**  ___ 1. Yes  __*-1.Don’t know***J16**  __ *-2. Refused*** J16** | ___ 0. No** J16**  ___ 1. Yes  __*-1.Don’t know***J16**  __ *-2. Refused*** J16** | ___ 0. No** J16**  ___ 1. Yes  __*-1.Don’t know***J16**  __ *-2. Refused*** J16** | ___ 0. No** J16**  ___ 1. Yes  __*-1.Don’t know***J16**  __ *-2. Refused*** J16** |

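### At follow-up, J12 has no time limit and J13 does not ask for the partner's most recent test, so re-tests are recorded only if the respondent happens to report the latest one

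*Protocol*

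**What the plan says.** Partner testing is an objective, a listed outcome variable (Variables, Primary Outcome Variables) and a directional 12-month hypothesis: "Increase in number of sex partner(s) getting an HIV test". The package targets re-tests as well as first tests. The lay counselor gives each patient "a slip to give to their partner if their partner has not been tested or needs to be re-tested" (HIV Prevention and Adherence Counseling by Lay Counselors).

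The patient interview (Appendix H, Patient Sex Behavior) asks about each of up to five recent partners, identified by J6 ("J6. What is the first name or a nickname of this partner"). "J12. Has this partner been tested for HIV" is answered yes or no. Every yes leads to "J13. How long ago was this partner tested for HIV", with space for one answer in days, months or years.

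The Data collection section says the same battery is used at 6 and 12 months, "with the exception of some of the sociodemographic questions and items asking about whether something had" ever happened. The printed form is headed "Baseline Questionnaire" but carries tick boxes for all three assessments. The Study design section lists partners' testing history among the topics covered at every assessment.

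**The concern.** The hypothesis is about testing that happens during the trial. J12 alone gives status at any time up to the interview: a partner tested before the package is a yes at every wave, and a re-test cannot change that. Only J13 can separate an old test from a new one, and it does not say which test it means when a partner has had more than one.

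At stake is whether the trial can see one of the two things its package does for partner testing. Re-testing matters chiefly for partners whose earlier result was negative, the people whom prevention with HIV-positive patients is meant to protect. An analysis plan can decide how to combine J12 and J13, but it cannot later recover which test the respondent had in mind.

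**Working it through.** The protocol gives no figure for this point, so there is nothing to reproduce. The check has four parts.

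**1. What each testing history leaves in the data (baseline to follow-up)**

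| Partner's history | J12 | J13 at follow-up | Seen as a test during the trial? |
|---|---|---|---|
| Untested at baseline, first test in trial | no to yes | short interval | Yes, from J12 alone if J6 links the partner |
| Tested before, re-tested, respondent dates the latest test | yes to yes | short interval | Yes |
| Tested before, re-tested, respondent dates the earlier test | yes to yes | long interval | No |
| Tested before, not re-tested | yes to yes | long interval | No (correct) |

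The third and fourth rows cannot be told apart. Which of rows two and three applies depends on how the respondent reads J13.

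**2. Wording elsewhere in Appendix H**

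Other items do specify the latest event: B4 (CD4 test), J9 (sex with the partner) and G7 (missed medication). Others set a six-month limit: K2, K4, K6 and K8, L1a to L3a, N3 and N7. J12 and J13 do neither.

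**3. Dating a test**

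Inputs from the Study timeline: baseline January to February 2009; training February to March 2009; 6-month follow-up September to October 2009; 12-month follow-up April to May 2010. Gaps in months (days / 30.4375), from the end of the earlier window to the start of the later one, and from start to end:

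- training to 6-month interview: 5.1 to 8.9
- 6- to 12-month interview: 5.0 to 8.9
- training to 12-month interview: 12.0 to 15.9
- baseline to 12-month interview: 13.0 to 16.9

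Answers in days or months can be set against these gaps. The coarse case is an answer of 1 year at the 12-month interview. Assume, for illustration only, that such an answer stands for any true interval from 6 to 18 months with equal probability. The share falling before a point g months back is (18 − g) / 12:

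- before training: (18 − 12.0) / 12 = 50% down to (18 − 15.9) / 12 = 17.5%
- before baseline: (18 − 13.0) / 12 = 42% down to (18 − 16.9) / 12 = 9%

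The rounding range is an assumption; the protocol does not give one. How many respondents would answer in years is also unknown.

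**4. Other records of partner tests**

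- Q6c and R8c ask whether the patient got partners tested after talking with providers or counselors. They are not limited to first tests. They are not asked per partner, they depend on a discussion with staff, and patients who met no counselor skip R8 altogether.
- The lay counselor record (Appendix L) has a partner-test box with date and place, but it is completed in intervention clinics.
- Returned slips track partners who come to the clinic for testing.
- The Clinic Services Form (Appendix O) counts all HIV tests in the clinic, not partners' tests.
- The chart review form (Appendix P), as printed, has no partner-test field outside the lay counselor record.

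These are useful support. None gives an equivalent per-partner measure in both arms.

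**The case against.** The strongest reply is that J13 follows every yes. A partner tested before baseline and re-tested two months before an interview can be recorded as tested two months ago, so a reader who infers that re-tests cannot register at all goes too far. This stands.

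The three waves also help. A test near the start of the package would be about 5 to 9 months old at the 6-month interview and could be reported then in months, and J6 allows a change from no to yes to be placed inside the trial. The one-year ambiguity therefore falls mainly on partners who were not covered at 6 months and whose test is dated in years. This stands too.

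The follow-up wording is not printed. That is a fair caution, but the protocol points to repetition: same battery, tick boxes for later waves, testing history at each assessment. If J12 were instead removed as an item about whether something ever happened, the follow-up interview would lose its partner-testing status question.

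It can also be said that the hypothesis counts partners rather than tests, and that the derivation may sit in the analysis plan. A partner re-tested during the trial is still a partner getting a test, and no derivation repairs an ambiguous answer. Finally, the trial is powered on unprotected sex, not on partner testing. That limits the weight of the point but does not remove it.

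**Conclusion.** The point holds as a measurement weakness in a listed outcome. Re-tests promoted by the package are captured only when the respondent happens to report the latest test, and an answer of one year ago at the 12-month interview does not by itself settle whether the test came before or after the package began. This assumes that J12 and J13 are carried into the follow-up forms unchanged.

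It is not a bias between arms. Clinics were randomised, so pre-package tests are balanced in expectation and an ever-tested comparison remains valid for what it measures, which is first tests.

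The size of the loss is unknown. A reader might infer a large one from an illustration such as this: 30% to 60% of partners tested at baseline, half of those HIV-negative, and a 15-point effect on both first tests and re-tests. First tests then contribute 0.70 × 15 = 10.5 to 0.40 × 15 = 6.0 points, and re-tests 0.30 × 0.5 × 15 = 2.25 to 0.60 × 0.5 × 15 = 4.5 points. The re-test share is 2.25 / 12.75 = 18% to 4.5 / 10.5 = 43%. The protocol does not support that as the expected loss. The baseline range and the effect have no source in it, the one-half borrows a Kenyan figure for spouses and cohabiting partners, and the calculation discards J13 entirely. It is at most an upper case for an outcome built on J12 alone.

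**What to change.** In the 6- and 12-month versions of Appendix H:

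- Reword J13 to: *How long ago was this partner's most recent HIV test?*
- Add directly after J12: *Since your last interview in [month/year], has this partner had an HIV test?* The interviewer fills in the date of the last completed interview.

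Use the new item for the 12-month partner-testing hypothesis, taking the 6- and 12-month answers together so that the whole period since baseline is covered. Keep ever-tested as a supporting measure. Do not restrict the denominator by a partner status learned after baseline: the package itself affects whether that status becomes known, so such a restriction could undo the balance that randomisation gives.

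The cost is one added and one reworded item per partner, their translation into the interview languages, and a sentence defining the outcome. No extra visits, staff or patients are needed. The change has to be made before the follow-up interviews.

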**[*REMEMBER: Turn back to J6 on Page 25 and fill out the next partner column if the patient has additional partners.]***

**Sex exchange**

| ***Interviewer reads: “***Now I would like to ask you questions about some other important aspects of a person's life. I know that some of these questions are very personal. However, your answers are crucial for helping to understand the condition of people in [COUNTRY]. Let me assure you that your answers are completely confidential and will not be told to anyone and no one else will know that you were asked these questions. If we should come to any question that you do not want to answer, just let me know and we will go on to the next question.” |
| --- |

|  | **No** | **Yes** | *Don’t know* | *Refused* |
| --- | --- | --- | --- | --- |
| K1. Have you ever had sex in order to get a place to stay? | 0  *Skip to K3* | 1 | *-1* | *-2* |
| K2.In the last 6 months, did you have sex in order to get a place to stay? | 0 | 1 | *-1* | *-2* |
| K3. Have you ever had sex to get money? | 0  *Skip to K5* | 1 | *-1* | *-2* |
| K4. In the last 6 months, did you have sex to get money? | 0 | 1 | *-1* | *-2* |
| K5. Have you ever had sex to get food? | 0  *Skip to K7* | 1 | *-1* | *-2* |
| K6. In the last 6 months, did you have sex to get food? | 0 | 1 | *-1* | *-2* |
| K7. Have you ever had sex to get gifts? | 0  *Skip to L1* | 1 | *-1* | *-2* |
| K8. In the last 6 months, did you have sex to get gifts? | 0 | 1 | *-1* | *-2* |

**Violence**

L1. Have any of your current partners hit, slapped, kicked, or done anything else to hurt you physically?

_____ 0. No  *Skip to L2*

_____ 1. Yes

*_____ -1. Don’t know*   *Skip to L2*

*_____ -2. Refused*   *Skip to L2*

*_____ -3. Not Applicable*  *Skip to L2*

L1a. Did this happen in the last 6 months?

_____ 0. No

_____ 1. Yes

*_____ -1. Don’t know*

*_____ -2. Refused*

L2. Has anyone else ever hit, slapped, kicked, or done anything else to hurt you physically?

_____ 0. No *Skip to L3*

_____ 1. Yes

*_____ -1. Don’t know*  *Skip to L3*

*_____ -2. Refused*  *Skip to L3*

L2a. Did this happen in the last 6 months?

_____ 0. No

_____ 1. Yes

*_____ -1. Don’t know*

*_____ -2. Refused*

L3. Has anyone ever forced you to have sexual intercourse or perform any other sexual acts?

_____ 0. No  *Skip to M1 in next section*

_____ 1. Yes

*_____ -1. Don’t know*  *Skip to M1 in next section*

*_____ -2. Refused*  *Skip to M1 in next section*

L3a. Did this happen in the last 6 months?

_____ 0. No

_____ 1. Yes

*_____ -1. Don’t know*

*_____ -2. Refused*

**Sexual Self-Efficacy**

| ***Interviewer reads:*** “The next items are about condom use.   - Please answer all items as they apply to your current situation. - If you have not had experience in the given situation, answer how you might feel about it.” |
| --- |

M1. I feel comfortable asking my partner(s) to use condoms.

_____ 0. No

_____ 1. Yes

*_____ -1. Don’t know*

*_____ -2. Refused*

M2. I know how to use male condoms correctly.

_____ 0. No

_____ 1. Yes

*_____ -1. Don’t know*

*_____ -2. Refused*

M3. I know how to use female condoms correctly.

_____ 0. No

_____ 1. Yes

*_____ -1. Don’t know*

*_____ -2. Refused*

M4. I can get enough male condoms to use them every time I have sex.

_____ 0. No

_____ 1. Yes

*_____ -1. Don’t know*

*_____ -2. Refused*

M5. I can get enough female condoms to use them every time I have sex.

_____ 0. No

_____ 1. Yes

*_____ -1. Don’t know*

*_____ -2. Refused*

M6. I can refuse to have sex with my partner if he/she does not want to use condoms.

_____ 0. No

_____ 1. Yes

*_____ -1. Don’t know*

*_____ -2. Refused*

**Sexually Transmitted Infections (STIs)**

| ***Interviewer reads:*** “These next few questions have to do with any experiences you have had with any infections in your private / genital area.” |
| --- |

N1. Have you ever had any of the following sexually transmitted infection symptoms*? [Read the following choices. Tick all that apply]*

_____ 1. Abnormal or unusual discharge from your vagina **(women only)**

_____ 2. Abnormal or unusual discharge from your penis **(men only)**

_____ 3. Sores in your genital area

_____ 4. Pain in your lower abdomen **(women only)**

*_____-1. Don’t know*

*_____-2. Refused*

*[If NO answer choice is ticked above, skip to P1f]*

N2. Have you ever been treated for a sexually transmitted infection or symptoms such as genital discharge, sores in your genital area, pain during urination, or (for women only) pain in your lower abdomen?

_____ 0. No

_____ 1. Yes

*_____-1. Don’t know*

*_____-2. Refused*

